### Trial procedures

Figure 1 provides a preliminary CONSORT diagram of the study and participant flow. Baseline and follow-up psychometric and biometric data from all patients will be obtained by trial nurses at two main community mental health clinics. However, it is expected that a small number of participants may not be physically able to travel to health clinics; if this should eventuate, trial nurses will make alternative arrangements to facilitate collection of participants’ data. Blood will be taken by trial nurses (trained in phlebotomy) and processed by a community health pathology provider or a Point of Care analysis machine (Roche *cobas® b 101*) able to provide on-the-spot blood results for total and HDL cholesterol, and a glucometer will provide blood glucose levels. Body mass index-based risk scoring will be used if bloods are unattainable. Digital scales and a stadiometer were to used in order to calculate BMI, while a Bedfont *piCO™ Smokerlyzer* will be used to determine the proportion of carboxyhemoglobin (%COHb) and blood carbon monoxide concentration in parts per million (COppm). All data from biometric and psycho-social measures will be entered into the survey application, *Qualtrics,* on a tablet. Full survey data will also backed-up by downloading weekly into a password secured, university file folder.

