### Outcomes measures

As shown in Fig. 2, outcome assessment at baseline, 6,12, 18 and 24 months: bloods and self-report outcomes will be collected by trial staff. Biometric measures constitute total and high cholesterol lipids, blood pressure, weight in kilogrammes, blood glucose level, height and waist measurement in centimetres, %COHb, blood COppm, which constitute the necessary information to calculate the General CVD Risk Score [31]. The self-report measures comprise quality of life [32] SF-12; psychological distress [33] K-10; the Alcohol Use Disorders Identification Test - consumption [34] AUDIT C-3; the Fagerström Test for Nicotine Dependence [35]; the Medical Outcomes Study Sleep measure [36] MOS Sleep; International Physical Activity Questionnaire [37] IPAQ; Australian dietary guidelines healthy eating quiz [38], Partners in Health [39, 40] PIH; Patient Assessment of Chronic Illness Care [41] PACIC; Singh O’Brien Level of Engagement Scale [42] SOLES. Hospital admissions will be extracted from service records to minimise burden on patients and health care staff.

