**Fig. 2 Fig2:**
[figure not shown]
Standard Protocol Items: Recommendations for Interventional Trials (SPIRIT) Figure of enrolment, treatment and assessments over time

Key outcomes will involve assessing change at 6, 12, 18 and 24 months for the following measures:Absolute CVD risk will be measured using the General CVD Risk Score [31]. This measure applies from age 30 years and includes gender, age, systolic blood pressure, smoking in last week (Y/N), diabetes (Y/N), hypertensive medication (Y/N), and either total and HDL cholesterol or body mass index (Aim 1, Hypothesis 1).Health-related quality of life will be measured by the SF-12 [32], a validated and commonly used instrument, producing summary scores for mental health and physical health components. The Australian SF-6D scoring algorithm developed by [name] and colleagues will be applied to generate utilities and calculate quality adjusted life years [43], (Aim 1, Hypotheses 2 and 3).

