### Statistical analysis

Data analyses will be undertaken using an *intention-to-treat* methodology, adhering to CONSORT guidelines. However, where necessary, analyses will also adopt a *per protocol* approach. The following processes have informed the sample size calculation for the 10-year CVD risk change score. Our pilot data (*n* = 17) found mean (SD) of 10-year risk to be 16.9% (9.8%). Thus, taking a conservative baseline mean CVD risk score of 10.5% and a proportionate SD of 6% and assuming a correlation of 0.5 between baseline and follow up scores, a sample of 304 (i.e., 152 per group), provides 80% power to detect a relative change of 20% in 10-year CVD risk. This calculation was achieved using Stata’s *sampsi* command. These changes are realistic; other current empirically-designed interventions providing coordination alone [44, 45] or self-management alone [46, 47] have achieved substantial levels of change. If necessary, we will transform non-normal data to meet normality conditions. The present intervention provides *both* coordination and self-management, and also includes management of CVD risk. We will sample a total of 358 participants allowing for an attrition rate of 15%. Linear regression will be employed to analyse primary outcomes, clustering over nurse delivering the intervention to account for possible correlated outcome measures. The dependent variable will be the outcome at follow-up. The independent variables will be the outcome at baseline and group assignment. Diagnostic tests to examine homoscedasticity and normality of residuals will be carried out to ensure model validity. The calculations for each primary outcome assume a Type I error rate of 2.5% to protect the overall Type I error rate of 5%. A three level random effects mixed models, using Stata’s *mixed* command will be used to analyse outcomes at several timepoints. If necessary, time will be reparametrised. Nurse, and individual within nurse, will be entered as random effects to account for correlated measures within an individual. The dependent variable will be the outcome at each timepoint. The independent variables will be group assignment, time and the product term group ‘x’ time. Differences between groups across time will be assessed via the interaction term. All results will be reported with 95% confidence intervals, and a *p*-value of less than 0.05 (two-tailed) will be deemed to be statistically significant. All analyses will use Stata (StataCorp, College Station, Texas).

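### The fallback from cholesterol to BMI lets a participant's baseline and follow-up CVD risk scores come from different formulas, and the planned models do not allow for it

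*Protocol article*

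**What the plan says.** The Hypothesis 1 outcome is absolute CVD risk by the General CVD Risk Score. Under Outcomes measures, after the caption of Fig. 2, the article lists inputs common to every calculation (gender, age, systolic pressure, smoking, diabetes, antihypertensive medication) and then an alternative: "and either total and HDL cholesterol or body mass index".

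Trial procedures says when the alternative applies: "Body mass index-based risk scoring will be used if bloods are unattainable". That sentence stands in a paragraph that opens with "Baseline and follow-up psychometric and biometric data from all patients will be obtained by trial nurses", so it is not confined to baseline.

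The outcome is followed over time: "Key outcomes will involve assessing change at 6, 12, 18 and 24 months". Under Statistical analysis, the regression for the primary outcomes is specified as follows: "The dependent variable will be the outcome at follow-up" and "The independent variables will be the outcome at baseline and group assignment". A three-level mixed model with group, time and their product covers several timepoints. Neither model has a term for score version.

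The inputs to BMI are scheduled measures in their own right: "weight in kilogrammes, blood glucose level, height and waist measurement in centimetres".

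**The concern.** The comparison rests on a follow-up score set against the same person's baseline score. If bloods are obtained at one visit and not at the other, the rule as stated lets the two scores come from different formulas. The difference between them then contains the disagreement between formulas as well as any change in risk.

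The two versions also respond to the programme through partly different inputs. The intervention covers both lipid medication and weight reduction (The Flinders Program intervention; Table 1). Lipids enter directly only in one version and BMI only in the other.

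Two consequences should be kept apart:

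- **Noise.** Mixed pairs add residual variance and lower the baseline to follow-up correlation. This happens even if switching is equally common in both arms.
- **Bias.** Follow-up bloods are missed after randomisation. If the frequency or direction of switching differed by arm, the mean gap between formulas would enter the treatment estimate. In the mixed model it would load on the group-by-time term used to judge the difference between groups.

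**Working it through.** **1. What the text permits.** The outcome definition allows two versions. The fallback is triggered by unattainable bloods, in a paragraph covering baseline and follow-up. The regression uses the follow-up and baseline scores without reference to version. Read together, these allow a mixed pair. The article does not say that the choice is made afresh at each visit; it also does not say that it is fixed per participant.

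**2. The plan's own sample size.** Inputs from Statistical analysis: baseline mean 10.5%, SD 6%, correlation 0.5, relative change 20%, 80% power, two-sided alpha 0.025 per primary outcome, 152 per group.

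- Target difference: 0.20 × 10.5 = 2.1 points.
- Variance of the change score: 2 × (1 − 0.5) × 36 = 36.
- n per group = 2 × 36 × (2.241 + 0.842)² / 2.1² = 155.2, so 156 per group or 312 in total, against 304 stated (within 3%). Power at 152 per group is 79.1%.
- 304 / (1 − 0.15) = 357.6, so 358, as stated.

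The stated figure is reproduced closely and contains no allowance for mixed versions. For the regression on baseline that is actually planned, the residual variance is (1 − 0.5²) × 36 = 27, and power at 152 per group is 90.0%.

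**3. Noise (illustration).** Assume that 15% of participants have a mixed pair and that the within-person SD of the gap between formulas is 3 points, with no mean gap. Neither figure is in the documents.

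- Added variance: 0.15 × 3² = 1.35.
- Relative to the planned model: 1.35 / 27 = 5%.
- Power on the baseline-adjusted model: 90.0% falls to 88.4%.
- Power on the change-score basis (36 + 1.35 = 37.35): 79.1% falls to 77.5%.

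Over a wider set of assumptions, added variance = q × SD² + q × (1 − q) × gap², where q is the share of mixed pairs:

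| Assumed q, mean gap, gap SD | Added variance | Power, change score | Power, baseline-adjusted |
|---|---|---|---|
| none | 0 | 79.1% | 90.0% |
| 5%, 0.5, 2 | 0.21 | 78.8% | 89.8% |
| 30%, 2, 4 | 5.64 | 72.4% | 83.2% |

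**4. Bias (illustration).** Bias = (difference in switching rate between arms) × (mean gap between formulas). Assume 5% switching in one arm, 15% in the other, all in the same direction, and a mean gap of 1 to 3 points.

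- 0.10 × 1 = 0.1 points and 0.10 × 3 = 0.3 points.
- Relative to target: 0.1 / 2.1 = 5% and 0.3 / 2.1 = 14%.
- Standard error on the planned model: √(2 × 27 / 152) = 0.60, so the bias is about 0.2 to 0.5 standard errors.

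Rate differences of 5 to 20 percentage points with gaps of 0.5 to 2 points give 0.025 to 0.4 points, or 1% to 19% of the target. With equal rates and similar gaps in both arms, this term is zero.

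**The case against.** The strongest reply is that this is a scoring detail for the full protocol or the analysis plan, neither of which is shown. That would hold if the article were silent. It is not: it states a fallback rule for a key outcome, and the rule as stated allows mixed pairs. An unseen document may add a consistency rule, and if so the point is closed by citing it.

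Four further objections stand, at least in part.

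- **Visit-by-visit switching.** A reader might infer that the rule is meant to work visit by visit. The text does not say so. It could have been written for people who never give blood.
- **Lipids against weight.** A reader might infer that lipid treatment moves only one version and weight loss only the other. That goes too far. Both versions share six inputs, so smoking cessation and blood pressure treatment register in both, and weight loss may also act through blood pressure, diabetes or lipids.
- **Differential switching.** It is tempting to conclude that the comparison is biased. The documents do not show that. Outcome bloods in both arms are collected by trial staff at the same scheduled times, with on-the-spot testing available. The six intervention follow-ups end at week 20 and may be by phone or message. What remains is plausibility: patients know their arm, and the nurses who collect trial data deliver the programme to one arm only.
- **The fallback has a benefit.** It keeps participants who would otherwise have no score.

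Samples may also be "processed by a community health pathology provider or a Point of Care analysis machine", so the cholesterol method could vary within a person. That is a separate matter of field procedure with no size attached, and it is not part of this point.

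**Conclusion.** The point holds as one of outcome definition. As written, baseline and follow-up scores for one participant may come from different formulas, and the planned models do not account for it. The sure consequence of any such pairs is added noise and a weaker baseline covariate. On the illustrative figures this is modest, at about 1.6 points of power with 15% mixed pairs. Bias is conditional on switching that differs by arm, which is possible but not demonstrated. Its size cannot be derived from the documents; 0.1 to 0.3 points of the 2.1-point target rests wholly on the assumed switching rates and formula gap. The sample size calculation is not in question here. The rule should be corrected because the remedy is cheap and uses scheduled data, and it should be settled before unblinding so that the choice of version cannot depend on the results.

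**What to change.** - **One version per participant within an analysis.** Use the cholesterol-based score if bloods are available at all visits entering that analysis, otherwise the BMI-based score at all of them. Apply this to both the regression and the mixed model. Choosing the version separately for each baseline and follow-up pair is not enough, because a participant could then change formula between visits within the mixed model.
- **Sensitivity analysis.** Compute the BMI-based score for all participants at every visit where BMI is available, and repeat the analysis. BMI is scheduled for everyone, but it may be missing for some who cannot attend a clinic.
- **Reporting.** Give the number of participants scored by each version, by arm.

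Cost: some observed lipid values go unused in the primary score for participants with incomplete bloods, and there is one extra analysis. No new measurement is needed. Requiring the same cholesterol assay within a participant would change field procedure and is not proposed; at most, the method used could be recorded.

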**Fig. 1 Fig1:**
[figure not shown]
Participant flow across two arms of the RCT

Post baseline, key patients’ details (Study ID, age, gender) will be sent to an independent clinical trials allocations unit who will be provided with computer-generated protocol for block randomising (i.e., stratified by age and gender) participants. Those randomised into the intervention arm will have their intervention delivered by trial nurses trained in the Flinders Program and study-specific interventions, as illustrated in Table 1. Once the initial Flinders Program assessments have been delivered (Cue & Response; Problems and Goals; see Additional file 2: Table S1), trial nurses will negotiate with participants whether contact is undertaken face-to-face or remotely (e.g., phone; email) on a case by case basis.

Expert Flinders Program trainers will monitor trial nurses by sampling care plans and will provide group and individual supervision initially weekly then monthly to maintain fidelity. Trial nurses will not provide services to ‘control’ group patients. For both groups, other services will continue as usual. However, if at any stage during the intervention, a given participant’s mental health declines to a level that warrants inpatient admission, or where they indicate that they do not wish to continue, s/he will be withdrawn from the trial without adverse impact on their usual care or relationship with the mental health services. The participant can elect to rejoin the trial once the problem is addressed. Post trial, data will be de-identified, and securely stored in a password protected university data repository. Subsequent requests for access to trial data will be considered and then approved/not approved by study CIs.

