### The Flinders Program intervention

The Flinders Program provides both framework and tools to engage the patient and structure self-management assessment, tailored planning, motivational enhancement, disease management, prevention, coordination and outcome measurement. It drives optimal use of current health services. In this trial, intervention-allocated participants will be supported to access existing structures and motivational processes including smoking cessation programs; clinical control of triglycerides and diabetes; one-on-one and group components of weight reduction programs; and, where applicable, initiation and adherence with BP-lowering and lipid medications.

Once training has been undertaken, any clinician can deliver the program; however, in the trial’s instance, mental health nurses will facilitate the intervention. Further, while the Flinders Program can be delivered face-to-face, it can also be provided by phone and/or electronically, according to patients’ needs. A web version of the program allows patients and trial nurses to develop the care plan either face-to-face or via the web. This permits communication in real time, or asynchronously via text or email, enabling monitoring and motivational enhancement. In circumstances where participants are randomised into the intervention and subsequently voice issues with continuing to participate in this group, accommodations are made for withdrawal from the intervention program. However, these participants are given the option to continue providing information at the scheduled follow-up data collection points. Details of intervention steps are provided in Table 1.

**Table 1 Tab1:** Summary of intervention schedule and components

Flinders Program component^a^	Planning and action for:	
	Condition management	CVD risk management

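### Withdrawing participants from the trial when admission is warranted or they do not wish to continue conflicts in part with the programme-only withdrawal described elsewhere, and weakens the intention-to-treat analysis

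*Protocol article*

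**What the plan says.** Three sections of the protocol article bear on who stays in follow-up, and a fourth on where admissions data come from.

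- **Trial procedures** (text after Fig. 1). The rule operates at any point while the intervention is under way. It covers a participant whose mental health "declines to a level that warrants inpatient admission, or where they indicate that they do not wish to continue, s/he will be withdrawn". The withdrawal is from the trial, not only from the programme: "s/he will be withdrawn from the trial without adverse impact on their usual care or relationship with the mental health services". The next sentence softens this: "The participant can elect to rejoin the trial once the problem is addressed".
- **The Flinders Program intervention.** For participants randomised to the intervention who raise problems with continuing, "accommodations are made for withdrawal from the intervention program", and "these participants are given the option to continue providing information at the scheduled follow-up data collection points".
- **Statistical analysis.** "Data analyses will be undertaken using an *intention-to-treat* methodology, adhering to CONSORT guidelines". A per-protocol approach is added where necessary.
- **Outcomes measures.** "Hospital admissions will be extracted from service records to minimise burden on patients and health care staff".

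**The concern.** Trial procedures makes leaving the trial the stated consequence of two events. For unwillingness to continue, the intervention section gives the opposite consequence for intervention participants: they leave the programme and follow-up stays open. Staff cannot apply both.

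For admission, the difficulty is one of effect. Needing admission happens after randomisation and is plausibly related to SF-12 scores. Intention-to-treat needs outcomes from everyone randomised. A rule that ends participation because of such an event can make outcomes missing for reasons tied to their values, and no analysis plan can recover data that were never collected.

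Quality of life is Hypothesis 2 under Aim 1, and SF-12-based utilities feed the cost-effectiveness result under Hypothesis 3, so both are exposed.

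**Working it through.** **1. The sections side by side**

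| Trigger | Trial procedures | Flinders Program intervention | Result |
|---|---|---|---|
| Does not wish to continue | Out of the trial; may rejoin | Out of the programme; may keep giving data (intervention arm) | Direct conflict |
| Decline warranting admission | Out of the trial; may rejoin | Not mentioned | No literal conflict, but outcome data may stop |

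**2. Timing.** Table 1 lists the last programme contact at week 20, and the first follow-up assessment is at 6 months. If the intervention period means the Table 1 contacts, a participant withdrawn in that period who does not rejoin has baseline data only. The main regression takes the follow-up outcome as its dependent variable, so that person contributes nothing to it. The care plan is said to cover 6 to 12 months and the trial is described as a 12-month one, so the period could also be read as longer. Some withdrawn participants would then have a 6-month value.

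**3. The plan's own figures.** Inputs from Statistical analysis: mean 10.5%, SD 6%, relative change 20%, correlation 0.5, alpha 2.5% (two-sided), power 80%, attrition 15%.

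- Difference: 0.20 × 10.5 = 2.1 points; 2.1/6 = 0.35 SD.
- Change-score SD: 6 × √(2 × (1 − 0.5)) = 6.
- Per arm: 2 × (2.2414 + 0.8416)² / 0.35² = 155.2, so 156, or 312 in total. This is within 3% of the stated 304. Power at 152 per arm is 79.1%.
- Attrition: 304/0.85 = 357.6, so 358, as stated.

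The sample size is not in dispute.

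**4. Size of a possible bias.** Let d be the SF-12 deficit, in SD, of those lost relative to the rest of their arm (taken as equal in both arms). Let p_I and p_C be the proportions withdrawn and not rejoining. The unadjusted shift in the between-arm difference is

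bias ≈ d × (p_I − p_C), positive in favour of the programme.

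The documents give neither d nor p, so these are assumptions:

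| d | p_I | p_C | Bias (SD) |
|---|---|---|---|
| 0.5 | 0.10 | 0 | 0.05 |
| 0.5 | 0.20 | 0 | 0.10 |
| 0.5 | 0.20 | 0.20 | 0 |
| 0.5 | 0.10 | 0.20 | −0.05 |

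Against the 0.35 SD design difference, the first two rows are 0.05/0.35 = 14% and 0.10/0.35 = 29%. (Against the difference detectable with 152 per arm, 3.083 × √(2/152) = 0.354 SD, they are 14% and 28%.) If half of those withdrawn rejoin, the shifts halve to 0.025 and 0.05 SD, or 7% and 14%. The yardstick was set for cardiovascular risk; the article gives none for SF-12.

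**5. Numbers and power.** With 358/2 = 179 per arm, 10% and 20% are 18 and 36 participants, against a 15% allowance of 27. If admission withdrawals came on top of the 15% in both arms and nobody rejoined, a further 5%, 10% or 20% would leave about 286, 269 or 233 evaluable. Change-score power for cardiovascular risk would fall from 79.1% to 76.4%, 73.4% or 66.6%. If the 15% already includes them, power is unchanged.

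**The case against.** The strongest reply is that the rule is milder than it looks. Participants may rejoin, so loss need not be permanent. Intention-to-treat is an analysis principle, and nothing says that withdrawn participants or their earlier data are left out. Missing-data handling commonly sits in an analysis plan, which is not shown. The regression adjusts for baseline and the mixed model uses earlier visits, which may absorb part of any bias.

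Much of this stands as a limit on size. It does not remove the problem. Rejoining is the participant's choice, so returners are self-selected and visits in between may be missed. The rule governs data collection, which an analysis plan cannot repair afterwards.

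Four stronger readings are tempting, and the documents do not support them:

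- **That only the intervention arm is affected.** The timing phrase suggests it, but the preceding sentence concerns both groups, the rule refers to participants generally, and it protects usual care, which both arms receive. Trial nurses see intervention participants more often, so decline might be noticed more in that arm, but this is an inference.
- **That admissions and their costs are lost.** Admissions come from service records, and nothing says extraction stops on withdrawal.
- **That the worst outcomes are removed generally.** This is plausible for SF-12 and psychological distress. A psychiatric admission does not by itself imply high 10-year cardiovascular risk.
- **That all three sections are mutually incompatible.** The direct conflict is confined to unwillingness to continue.

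**Conclusion.** The point holds in a limited form. The two withdrawal provisions conflict for intervention participants who do not wish to continue. The admission provision ends trial participation on a prognosis-related event after randomisation, which opens quality of life and the economic result to informative missingness and undermines the intention-to-treat commitment.

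If both arms are covered, the direction of bias is not established. If only the intervention arm is covered and those lost score worse, the bias favours the programme. The 0.05 to 0.10 SD illustration is towards the unfavourable end: it rests on an assumed 10% to 20% loss in one arm, none in the other, no rejoining, an assumed 0.5 SD deficit and no adjustment. Rejoining or control withdrawals would shrink it. No bias in cardiovascular risk is shown, and the stated sample size stands.

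**What to change.** Reconcile Trial procedures, the intervention section and Statistical analysis with one statement:

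- Neither admission nor leaving the programme by itself ends outcome follow-up.
- In both arms, scheduled assessments continue, delayed if needed, and service-record extraction continues, unless the participant withdraws consent for data.
- All participants are analysed as randomised.

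Decisions about the intervention itself stay with the clinicians and are not part of this change.

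The cost is a wording change and a few rescheduled visits by existing staff. Record extraction is already planned.
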